### Rescue, Failure, and Crossover Criteria

The independent attending physician may change modality or escalate care if deterioration occurs. To standardize decisions, treatment failure is defined by any of the following: persistent or worsening acidosis (pH decrease ≥0.03 from baseline or pH <7.25 with respiratory rate of >30 breaths per minute after 30 minutes of therapy, PaCO_2_ increase ≥5 mm Hg at 30 minutes compared with baseline, and SpO_2_ persistently below target for >5 minutes despite FiO _2_≥0.8 [or the maximal tolerated settings]), severe intolerance to the device (eg, sustained agitation or inability to tolerate the interface) despite comfort measures, and clinical signs of impending respiratory failure (eg, decreasing consciousness, marked fatigue, and hemodynamic deterioration). Intubation criteria follow departmental standards for acute respiratory failure and will be applied consistently in both arms. All crossovers and intubations will be recorded with timing and reason.

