### Outcome Measures

The primary outcome is the percentage change in PaCO_2_ from baseline to 60 minutes after initiation of therapy. Baseline is defined as the pretreatment ABG obtained before initiation of the assigned therapy (HVNI or NIPPV). This ensures that the primary outcome reflects the ventilatory effect of the intervention itself. The 30- and 60-minute assessment time points are measured from the time of therapy initiation. The ABG results and other variables (Table 1) to be collected will be documented in real time on paper-based CRFs by trained study investigators.

**Table 1. T1:** Summary of recorded patient variables in a noninferiority randomized controlled trial comparing high-velocity nasal insufflation (HVNI) vs noninvasive positive pressure ventilation (NIPPV) for type 2 respiratory failure in adult emergency department patients at National University Hospital, Singapore.

Variables	Measure
Primary outcome measure	Change in PaCO_2_^a^ at 60 min obtained after initiation of HVNI or NIPPV compared to baseline (before initiation of therapy)
Secondary outcome measures	Change in PaCO_2_ at 30 min compared to baseline Changes in respiratory rate 30 and 60 min after initiation of HVNI or NIPPV Modified Borg Dyspnea Scale at 30 and 60 min Treatment failure Conversion to another modality of oxygenation Requirement for intubation in the emergency department Adverse events due to therapy
Demographics	Age Gender Ethnicity BMI
Comorbidities	Congestive cardiac failure Ischemic heart disease Atrial fibrillation Chronic obstructive pulmonary disease Asthma Obstructive sleep apnea Diabetes mellitus Bronchiectasis Restrictive lung disease Neuromuscular disease Opioid or benzodiazepine use
Vital signs	Temperature Heart rate Respiratory rate Systolic and diastolic blood pressure Mean arterial pressure Glasgow Coma Scale
Investigations	Chest x-ray findings Arterial blood gas results at 0, 30, and 60 min
Clinical course and secondary clinical outcomes	Emergency department diagnosis Hospital inpatient discharge diagnosis Length of intensive care unit stay (if any) Length of hospital stay Inpatient mortality

a PaCO_2_: partial pressure of carbon dioxide.

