Percentage change (relative difference) as the primary outcome was selected to account for the wide range of baseline PaCO_2_ values expected in a heterogeneous, all-cause T2RF population. An absolute change in PaCO_2_ may disproportionately favor patients with higher baseline values as they have greater room for absolute reduction. The percentage change normalizes the treatment effect relative to each patient’s starting value, facilitating more equitable comparison across the spectrum of disease severity. To address the potential limitation of relative outcomes, a prespecified sensitivity analysis using absolute change in PaCO_2_ at 60 minutes will be conducted to confirm the robustness of the primary finding.

Secondary outcomes include the following: percentage change in PaCO_2_ from baseline to 30 minutes; change in respiratory rate at 30 and 60 minutes; modified Borg Dyspnea Scale (0-10) at 30 and 60 minutes [24]; proportion of treatment failure (as defined above), conversion to another modality of oxygenation, and need for intubation in the ED; adverse events due to therapy rendered (eg, facial pressure injury, vomiting, or aspiration); length of intensive care unit (ICU) and hospital stay; and inpatient mortality. Inpatient mortality will be assessed at hospital discharge. ICU length of stay (if applicable) and total hospital length of stay will be recorded in days from the date of ED presentation to the date of ICU discharge and hospital discharge, respectively. These data will be abstracted from the electronic health record (EHR) following patient discharge.

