### Statistical Analysis Overview

The primary analysis will follow an intention-to-treat approach, with supportive per-protocol analysis excluding major deviations (eg, early crossovers or missing postbaseline ABG values) and a safety set analyzed as treated. The main end point, percentage change in PaCO_2_ at 60 minutes, will be assessed using analysis of covariance (ANCOVA) adjusting for baseline PaCO_2_ and prespecified covariates (eg, etiology, baseline pH, and age). Noninferiority will be concluded if the upper bound of the 2-sided 95% CI for the HVNI–NIPPV adjusted difference is below the 4.3% margin. A prespecified sensitivity analysis will repeat the primary ANCOVA model using absolute change in PaCO_2_ at 60 minutes as the dependent variable to assess whether the conclusions are robust to the choice of relative vs absolute outcome metric. Secondary endpoints (percentage PaCO_2_ changes at 30 minutes, respiratory rate, and modified Borg Dyspnea Scale) will use similar adjusted models, whereas binary outcomes (treatment failure, intubation, and adverse events) will be compared using chi-square or Fisher exact tests and logistic regression, and length of stay and mortality will be assessed via nonparametric or time-to-event and logistic methods. Missing data handling will focus primarily on the primary outcome (percentage change in PaCO_2_ at 60 minutes). Missing 60-minute ABG results may occur due to early treatment crossover, intubation before the 60-minute time point, patient refusal of repeat ABG, or technical failure of the ABG analyzer. Multiple imputation by chained equations will be performed, with the imputation model including baseline PaCO_2_, baseline pH, treatment arm, age, etiology, respiratory rate, and 30-minute PaCO_2_ (if available). A minimum of 20 imputed datasets will be generated, and results will be pooled using the Rubin rules.

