### Quality Assurance and Monitoring

Study investigators will undergo training on device application, titration protocols, mask fitting and leak management, and CRF completion. An independent data monitoring and safety team within the institution will conduct periodic reviews to assess protocol adherence, data completeness, and safety. Any serious adverse events related to the study interventions will be reported to the National Healthcare Group Domain Specific Review Board per institutional requirements. Quarterly adherence checks will include verification of device settings, oxygen targets, ABG timing windows, and documentation of cointerventions.

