## Discussion

At comparable oxygen flow settings, HVNI may generate higher airway velocities than conventional high-flow nasal oxygenation, potentially improving ventilatory support while using similar oxygen flow. These characteristics could translate into operational and sustainability advantages if supported by measured reductions in cumulative oxygen consumption and resource use in clinical practice. In this trial, oxygen use and related resource metrics will be measured to substantiate any such claims.

If HVNI is found to be noninferior to NIPPV, it could offer a practical alternative in scenarios where mask-based interfaces are poorly tolerated or contraindicated. Potential advantages include fewer mask-related skin injuries, improved ability to communicate and take oral medications, and easier access for airway toileting and suctioning. These hypotheses will be evaluated alongside safety outcomes, recognizing that HVNI can have its own adverse effects (eg, nasal discomfort, mucosal dryness, and epistaxis) and that aspiration risk requires vigilance despite facilitated suctioning. Infection prevention measures appropriate for high-flow therapies will be followed in accordance with institutional policies.

In this study, HVNI will be delivered via a single-prong cannula (Unicorn) as a novel treatment for T2RF from all causes. We hypothesize that, through generation of nasopharyngeal pressure and high-velocity flow, HVNI may enhance extrathoracic dead-space washout and reduce PaCO_2_, achieving ventilatory effectiveness that is noninferior to NIPPV in acute T2RF. Device setup, flow titration, and monitoring will be standardized, with staff training to promote consistent delivery and protocol fidelity.

This trial builds on existing work in several ways. A prior study on single-prong nasal oxygenation focused largely on symptom relief in patients with COPD rather than ventilatory effectiveness in T2RF [15]. Randomized comparisons of HVNI and NIPPV in T2RF have predominantly enrolled COPD populations [11]. By evaluating ventilatory outcomes via a single-prong interface and enrolling patients with T2RF from any cause, this study addresses gaps in the literature and reflects the diagnostic heterogeneity commonly encountered in emergency care.

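### The adverse event comparison counts only therapy-attributed events in an open-label trial, and the as-treated safety set has no stated rule for patients who switch device

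*Protocol article*

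**What the plan says.** Statistical Analysis Overview (Protocol article) sets the analysis populations in one sentence. "The primary analysis will follow an intention-to-treat approach", a per-protocol analysis supports it, and there is to be "a safety set analyzed as treated". Intention-to-treat is attached to the primary analysis only.

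Outcome Measures defines the harm outcome twice, each time with a causality condition. Table 1 lists "Adverse events due to therapy", and the text lists "adverse events due to therapy rendered (eg, facial pressure injury, vomiting, or aspiration" and closes the bracket there.

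Rescue, Failure, and Crossover Criteria makes a change of device part of the design: "The independent attending physician may change modality or escalate care if deterioration occurs". It also states that "All crossovers and intubations will be recorded with timing and reason".

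The Blinding section says that participants, treating clinicians and bedside nurses know the allocation. The Discussion adds that research staff cannot be blinded either. Only the data analyst works with coded arms.

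**The concern.** Two choices affect the comparison of harms.

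**Attribution.** In acute hypercapnic failure, vomiting, aspiration or deterioration can be ascribed either to the illness or to the device. If an event counts only when someone judges it due to therapy, the count depends on that judgement. The coded dataset does not help, because the filter has acted before the analyst receives it. Nor can an analysis plan recover events that were never recorded. The Discussion accepts that lack of blinding may affect subjective measures. The mitigations it lists are an objective primary end point, standardized blood gas timing, escalation criteria and two analysis sets. None of them touches adverse event attribution.

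**Allocation of events after a switch.** Patients who deteriorate are the ones most likely to have had both devices. For them, as-treated has at least three meanings: first device, last device, or device in use at onset. Under the second or third, a complication that follows failure of one device is charged to the other.

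At stake is the safety description that will accompany the noninferiority result. The Discussion says the hypotheses will be evaluated alongside safety outcomes. With 42 patients per arm, two or three events can change that description.

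**Working it through.** The article gives no crossover rate and no adverse event rate, so it has no figure of its own to reproduce on this point. The only design input is 42 patients per arm (Sample Size). Everything else below is an assumption, shown over a range.

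**Allocation of events**

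Notation:
- c = proportion switching from HVNI to NIPPV
- d = proportion switching from NIPPV to HVNI
- r0 = event risk without a switch, taken as 10%
- r1 = event risk in those who switch, taken as 30% or 40%

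Difference, HVNI minus NIPPV:
- by randomized arm: (c − d)(r1 − r0)
- by last device: (r1 − r0) × [d/(1 − c + d) − c/(1 − d + c)]
- by first device: the same as by randomized arm, if all patients start as assigned

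Worked case, c = 20%, d = 0, r1 = 40%:
- Randomized arm: HVNI (33.6 × 0.10 + 8.4 × 0.40)/42 = 16.0%, NIPPV 10.0%, difference +6.0 points.
- Last device: HVNI 3.36/33.6 = 10.0%, NIPPV (4.2 + 3.36)/50.4 = 15.0%, difference −5.0 points.

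| c | d | r1 | Randomized arm (points) | Last device (points) |
|---|---|---|---|---|
| 10% | 0 | 30% | +2.0 | −1.8 |
| 20% | 0 | 40% | +6.0 | −5.0 |
| 30% | 0 | 40% | +9.0 | −6.9 |
| 10% | 5% | 30% | +1.0 | −0.9 |
| 30% | 5% | 40% | +7.5 | −5.2 |
| 20% | 10% | 40% | +3.0 | −2.1 |
| 10% | 10% | 40% | 0 | 0 |
| 0 | 20% | 40% | −6.0 | +5.0 |

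The last row is the second row with the arms exchanged. If r1 = r0, both columns are zero whatever the crossover.

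The same point in whole patients, by device at onset: suppose 6 of 42 HVNI patients switch and 3 have an event afterwards. By randomized arm these add 3/42 = 7.1% to HVNI. By device at onset they add nothing to HVNI and 3/(42 + 6) = 6.3% to NIPPV.

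**Attribution**

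Let both arms have the same all-cause risk p, with proportions aH and aN of events judged due to therapy. The observed difference is p(aH − aN), although the true difference is zero. It vanishes only if attribution is equal in the two arms. The article gives no means of estimating aH or aN, so this part cannot be sized.

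**Which outcomes are exposed**

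Outcome Measures lists treatment failure, conversion to another modality, ED intubation and inpatient mortality without any causality condition. The attribution problem does not reach them. Their analysis set is not stated, but nothing ties them to the as-treated set.

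**The case against.** The strongest reply is that as-treated is a common convention for safety sets and often means the treatment first received. On that reading nothing moves between arms. The rule for switched patients may also stand in an analysis plan that is not shown. This is right as far as it goes: reallocation of events is conditional on a reading that the article neither states nor excludes. It does not answer the causality filter, which is part of the stated outcome definition.

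A second reply is that the gravest consequences of device failure are captured anyway through failure, conversion, intubation and mortality. This also stands and limits the reach of the point. Events such as aspiration, vomiting and skin injury remain under the filter.

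Third, the article does not say that unblinded staff judge causality. Trained data entry staff outside clinical care abstract outcomes, and an independent monitoring and safety team reviews safety periodically. Unblinded attribution is therefore an inference, though a fair one: the bedside staff know the device, and neither the abstractors nor the monitoring team is described as blinded or as adjudicating cause.

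A reader might also infer more than the text supports:
- **That the plan favors HVNI.** The failure criteria apply to both arms and no crossover rate is given, so the direction is not fixed.
- **That nasal harms go uncollected.** The list in Outcome Measures is only illustrative, the case report form is not shown, and the Discussion takes up the issue, "recognizing that HVNI can have its own adverse effects (eg, nasal discomfort, mucosal dryness, and epistaxis" among its examples.
- **That serious events are filtered in the analysis.** The sentence "Any serious adverse events related to the study interventions will be reported" concerns notification of the ethics board, not the analyzed outcome.
- **That noninferiority depends on acceptable safety.** It is concluded from the confidence interval alone. The Discussion links acceptable safety and tolerance to whether further trials are warranted.

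**Conclusion.** The point holds in a limited form. As written, the adverse event outcome depends on attribution in an open-label trial with no blinded judgement described, so the comparison of harms can be biased by an amount and in a direction that the article does not allow one to estimate. The as-treated set adds a second, conditional problem. Under a current- or last-device reading, the sign of the difference can reverse: under the assumed rates with crossover from HVNI only, +2 to +9 points becomes −1.8 to −6.9. Under a first-device reading, equal crossover in both directions, or no excess risk in those who switch, there is no shift.

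The primary noninferiority analysis and the sample size are unaffected, and so is the definition of the four outcomes that carry no causality condition. The change is worth making because the remedy is simple and most of the data are still to be collected.

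**What to change.** Make the main safety comparison by randomized arm. Count all prespecified adverse events within a fixed window, whether or not they are attributed to therapy and whichever device is in use at onset. Record them on one checklist, identical in both arms, that names the mask-related and the nasal harms. Keep two supportive tables: events by device at onset, with that rule stated as the meaning of as-treated, and events judged related to therapy.

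The cost is a sentence or two in the analysis section and one case report form page. Crossover timing and reason are already to be recorded, so both tabulations are feasible. As of July 2026, 19 of 84 patients had been enrolled, which leaves 84 − 19 = 65 to be recorded prospectively. For those already enrolled, events may have to be retrieved from the record. The other downside is that more background events from the underlying illness will be tabulated in both arms.

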### Sample Size

A total of 84 patients (42 per group) will be enrolled to provide 80% power and one-sided α of 2.5% to demonstrate noninferiority [25] assuming an SD of 6.65% for percentage change in PaCO_2_ levels before and after treatment [26] and a noninferiority margin of 4.3%. The sample size includes an estimated 10% allowance for missing primary end point data. The noninferiority margin of a 4.3% absolute difference in percentage change was informed by clinician judgment (number of specialist accredited [board-certified] emergency physicians, n=14) of clinically acceptable differences and literature on PaCO_2_ responses to NIPPV. For example, emergency physicians opined that a change from 70 mm Hg to 63 mm Hg using HVNI (−10.0%) was considered noninferior to a change in PaCO_2_ from 70 mm Hg to 60 mm Hg after treatment with NIPPV (−14.3%).

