Sensitivity analyses will include (1) complete-case analysis (excluding participants with missing primary outcome data) and (2) worst-case imputation for the HVNI arm (assigning the worst observed percentage change to missing values in the HVNI arm and the best observed percentage change to missing values in the NIPPV arm), which is a conservative approach for noninferiority trials. Baseline covariates with missing data (expected to be minimal) will be handled through multiple imputation within the same multiple imputation by chained equations framework. Missing secondary outcomes will be analyzed using available data, with the extent of missingness reported for each outcome. Secondary endpoints will be treated as exploratory without formal multiplicity adjustment.

Prespecified exploratory subgroup analyses will be conducted to assess potential heterogeneity of treatment effect. Subgroups will include (1) COPD vs non-COPD etiology, (2) baseline PaCO_2_ strata (eg, 45‐60 mm Hg vs >60 mm Hg), and (3) baseline pH strata (eg, 7.25‐7.35 vs <7.25). Subgroup effects will be evaluated by including interaction terms (subgroup × treatment) in the primary ANCOVA model. These analyses are exploratory and hypothesis generating; the trial is not powered for subgroup comparisons, and results will be interpreted with caution.

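### The length-of-stay analysis leaves its method open and has no rule for in-hospital deaths; if a stay is closed at death, the arm with more deaths can look better (minor)

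*Protocol article*

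**What the plan says.** Outcome Measures defines stay in hospital, with ICU stay (where there is one) handled in the same way: "total hospital length of stay will be recorded in days from the date of ED presentation to the date of ICU discharge and hospital discharge," so that each stay runs to its own discharge date. The same section adds: "Inpatient mortality will be assessed at hospital discharge". Neither sentence says what value of stay a patient who dies receives.

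The Statistical Analysis Overview gives the analysis in one clause: "length of stay and mortality will be assessed via nonparametric or time-to-event and logistic methods". Read naturally, the first two families are for stay and logistic methods are for mortality. The section does not choose between a nonparametric and a time-to-event method, and it states no rule for censoring, competing events or ranking.

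Two further statements in that section bear on the point. On incomplete data: "Missing secondary outcomes will be analyzed using available data, with the extent of missingness reported for each outcome". On status: "Secondary endpoints will be treated as exploratory without formal multiplicity adjustment".

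**The concern.** Deaths in hospital are to be expected. Participants have acute hypercapnic acidosis, patients with do-not-resuscitate orders may enter if NIPPV is permitted, and inpatient mortality is itself an outcome. Death prevents discharge alive, so a comparison of stay needs a rule for it.

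Without one, the article's wording can be applied in several ways:

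- The stay is closed at the date of death. An early death then becomes a short stay, which a rank test reads as favourable.
- A patient who died has no discharge date, so the value is missing and the patient drops out under the available-data rule.
- In a time-to-event analysis the patient is censored at death, and is treated as if discharge would have followed later, as in survivors.
- Death is ranked worst, or kept as never discharged. This needs a rule that the article does not state.

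The same data can point in opposite directions under the first and the last of these. The Discussion says that the surrogate primary endpoint will be interpreted together with the secondary outcomes, so a stay result distorted by deaths could colour that interpretation.

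**Working it through.** **The plan's own figures.** The article gives no number for stay or mortality. Its sample size matters here only as the arm size: "A total of 84 patients (42 per group) will be enrolled to provide 80% power and one-sided α of 2.5"%. With SD 6.65 and margin 4.3, n = 2 × (1.960 + 0.842)² × 6.65² / 4.3² = 37.5, so 38 per arm. Adding 10% gives 38 × 1.10 = 41.8, so 42 per arm and 84 in total, as stated. (Dividing by 0.90 would give 43 per arm, 86 in total.) I use 42 per arm below.

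**Assumptions, none from the documents.** Survivors have the same stay in both arms: lognormal, median 7 days, SD of the log 0.7. Deaths occur early: median 2 days, SD of the log 0.7, with the same timing in both arms. Mortality is 10% on NIPPV and 10%, 20% or 30% on HVNI.

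**Direction, in closed form.** Let p1 and p0 be mortality on HVNI and NIPPV, and q the probability that the recorded stay of a patient who died exceeds that of a survivor. Then

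P(HVNI stay longer) = 0.5 + (p1 − p0) × (q − 0.5).

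- Stay closed at death: ln(7/2) / (0.7 × √2) = 1.253 / 0.990 = 1.27, so q is about 0.10. With 20% against 10%: 0.5 + 0.10 × (−0.40) = 0.46. With 30% against 10%: 0.5 + 0.20 × (−0.40) = 0.42. Both wrongly favour HVNI.
- Deaths ranked worst: q = 1, giving 0.55 and 0.60, against HVNI.
- Equal mortality: p1 − p0 = 0, so the result is 0.5 under either rule.

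The formula also shows that the direction depends on deaths coming early (q below 0.5).

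**Simulation.** 1,500 trials per scenario, stays rounded up to whole days, two-sided 5% tests (nominal 2.5% in each direction). Entries are the percentage of trials with HVNI significantly shorter / significantly longer.

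| Handling of deaths | 10% v 10% | 20% v 10% | 30% v 10% |
|---|---|---|---|
| Rank test, stay closed at death | 2.2 / 2.7 | 9.1 / 0.7 | 23.6 / 0.1 |
| Log-rank, death counted as discharge | 2.5 / 3.0 | 7.1 / 1.5 | 15.5 / 0.1 |
| Rank test, survivors only | 2.0 / 2.9 | 2.0 / 3.3 | 2.5 / 2.4 |
| Log-rank, censored at death | 2.7 / 3.0 | 2.1 / 4.3 | 1.4 / 3.2 |
| Rank test, deaths ranked worst | 2.3 / 2.5 | 0.2 / 12.1 | 0.0 / 37.3 |
| Log-rank, deaths never discharged | 2.3 / 2.9 | 0.2 / 20.1 | 0.0 / 57.7 |

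With stay closed at death, the average sample medians (HVNI v NIPPV) were 6.35 v 6.95 days at 20% v 10%, and 5.64 v 6.95 days at 30% v 10%. The simulated P(HVNI longer) was 0.462 and 0.422, in line with the formula.

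**A second set of assumptions.** With survivors at a median of 6 days and deaths at 2.5 days, the rank test with stay closed at death is significant in the wrong direction in 7.3% of trials for 20% v 10% mortality, and in 11.7% for 30% v 15%. The mechanism is the same and the effect smaller.

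**The case against.** The strongest reply is that this is an omission and not an error. The document is a condensed article, the section is headed as an overview, and a separate analysis plan may deal with deaths. Both remedies below already lie within the named families: time to discharge alive with death as a competing event is a time-to-event method, and a rank test with deaths ranked worst is nonparametric. Stay is exploratory, mortality has its own analysis, and a doubling of deaths would be visible beside the stay result. The figures rest on an assumed mortality difference and assumed early deaths.

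Most of this stands, and it sets the limits of the point. A reader might infer that the plan counts early deaths as short stays, or that neither listed method could treat death as the worse result. The documents support neither inference: no sentence says that death closes a stay, and both families contain a suitable version. Nor does bias follow on every reading, since survivors-only and censored analyses do not make the higher-mortality arm look shorter. They do show roughly no difference where one arm has more deaths.

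What remains is that the article does set out a stay definition and an analysis, and that the open choice covers methods that can disagree in direction. Death counts as the worse result only if a rule is added.

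**Conclusion.** The concern holds as a minor point. The article leaves open both the method for comparing stay and the place of in-hospital deaths in it. If stays are closed at death and compared by a plain rank test, the arm with more early deaths can appear to leave hospital sooner. Wrong-direction significance was about 7% to 24% against a nominal 2.5% across the assumed unequal-mortality scenarios. Dropping or censoring deaths brings this back to about nominal (1.4% to 2.5%) but conceals the difference. With equal mortality and equal timing of deaths there is no bias.

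The sizes are illustrations and not predictions: the documents give no mortality rate, stay distribution or time of death, and nothing in them suggests that HVNI raises mortality. The PaCO2 noninferiority conclusion does not depend on this.

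**What to change.** In the Statistical Analysis Overview, replace the open choice with one named analysis that applies to both hospital and ICU stay. Either of these would serve:

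- time to discharge alive, with inpatient death as a competing event, so that patients who die are kept as never discharged; or
- a rank test in which inpatient deaths receive the worst rank.

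Report stay in survivors as description only, next to mortality by arm.

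The cost is a sentence or two. The analysis needs the discharge dates and inpatient death status, which are already to be abstracted from the electronic health record, and the article says that analysis starts only after enrolment is complete (19 of 84 enrolled as of July 2026). The downside is that the result is a little less direct to read than a median stay in days; the descriptive figure for survivors partly makes up for that.

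### The stated imputation model leaves out the crossover and intubation events named as causes of missing 60-minute gases, and no planned sensitivity analysis lies between dropping those patients and an extreme bound

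*Protocol article*

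**What the plan says.** All references are to the Protocol article, Methods.

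- **Why data go missing** (Statistical Analysis Overview): "Missing 60-minute ABG results may occur due to early treatment crossover, intubation before the 60-minute time point, patient refusal of repeat ABG", with analyzer failure as a further cause.
- **Primary handling** (same section): multiple imputation by chained equations, at least 20 datasets, "with the imputation model including baseline PaCO_2_, baseline pH, treatment arm, age, etiology, respiratory rate, and 30-minute PaCO_2_ (if available". The time point of the respiratory rate is not given.
- **Missing-data sensitivity analyses** (same section): a complete-case analysis, and a single-value imputation that assigns the "worst observed percentage change to missing values in the HVNI arm and the best observed percentage change to missing values" in the NIPPV arm. The plan calls the second conservative.
- **Per-protocol set** (same section): leaves out early crossovers and patients without a post-baseline gas.
- **Decision rule** (same section): "Noninferiority will be concluded if the upper bound of the 2-sided 95% CI for the HVNI–NIPPV adjusted difference is below the 4.3% margin".
- **Data available** (Rescue, Failure, and Crossover Criteria; Outcome Measures): crossovers and intubations are logged with time and reason, and treatment failure is a secondary outcome.
- **Expected missingness** (Sample Size): a 10% allowance is built into the 84 patients.

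**The concern.** Two of the four stated causes of a missing primary outcome are events on the failure pathway. An imputation model without those events treats a patient who was intubated at 20 minutes like any other patient in that arm with similar baseline values. A 30-minute PaCO2 would correct much of this, but it enters only when it exists, and the earliest failures are the likeliest to lack it.

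The other planned analyses do not fill the gap. Complete-case and per-protocol analyses remove these patients. Worst/best imputation goes to the opposite extreme and gives every missing value, whatever its cause, the most unfavourable figure. A reader could be left with several analyses that ignore why data are missing and one that fails so often under equal arms that its failure says little. None shows how poor the missing values would have to be to change the conclusion. That matters in a noninferiority trial decided on 4.3 points.

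**Working it through.** **Inputs.** 42 per arm, 80% power, one-sided 2.5% ("A total of 84 patients (42 per group) will be enrolled to provide 80% power and one-sided α of 2.5% to demonstrate noninferiority"); SD 6.65 points ("assuming an SD of 6.65% for percentage change in PaCO_2_ levels before and after treatment"); margin 4.3 points ("The noninferiority margin of a 4.3% absolute difference in percentage change"); 10% missing, which is about 4 of 42 per arm. The true difference is not stated and is taken as 0, which reproduces the plan's sample size.

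**Step 1: the plan's own figure.** n per arm = 2 × (1.960 + 0.842)² × 6.65² / 4.3² = 37.5, so 38. Adding 10% gives 38 × 1.10 = 41.8, so 42 per arm and 84 in total. The stated figure reproduces.

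**Step 2: how worst/best imputation behaves when the arms are equal.** Simulation with 10,000 to 20,000 trials per setting: normal outcomes, SD 6.65, true difference 0, missingness unrelated to outcome. HVNI gaps take the HVNI arm's worst observed value and NIPPV gaps the NIPPV arm's best. Noninferiority is declared if the upper 95% limit is below 4.3.

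| Missing per arm | Complete case: noninferior | Worst/best: noninferior | Worst/best: fails | Mean shift in difference |
|---|---|---|---|---|
| 0 | 84% | 84% | 16% | 0 |
| 1 | 82% | 65–66% | 34–35% | 0.7 |
| 2 (5%) | 81–82% | 44–45% | 55–56% | 1.4 |
| 3 | 80–81% | 27% | 73% | 2.0–2.1 |
| 4 (10%) | 79–80% | 15% | 85% | 2.7 |
| 5 | 78–79% | 8% | 92% | 3.4 |

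The reason is simple. At 4 per arm the rule moves the difference by 2.7 points (2.7 / 4.3 = 63% of the margin) and raises its standard error to about 1.67. The typical upper limit is then 2.7 + 1.99 × 1.67 = 6.0, well above 4.3.

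Variations at about 10% missing:
- Covariates explaining 20% or 40% of the variance: fails in 84% or 82%.
- Eight missing, split 6/2 or 2/6: 84%. Split 8/0: 81%.
- Extremes taken across both arms: 94%.
- HVNI truly 2 points better, 4 missing per arm: still fails in about 43%.

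With only 4 missing in the whole trial, all in one arm, it fails in 53–54%.

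**Step 3: possible bias in the primary analysis.** Bias in the HVNI mean ≈ (share of HVNI patients missing because of failure) × (gap between their true value and the imputed one). The documents give neither term, so these are assumptions:
- 4 of 42 missing through failure, with values 7 points worse than imputed: 4/42 × 7 = 0.67. With 13.3 points worse: 4/42 × 13.3 = 1.27.
- 10% failing with a 21.4-point gap, partly recovered through a 30-minute PaCO2 correlated ρ with the 60-minute value: 0.10 × 21.4 × (1 − ρ) = 1.1, 0.6 and 0.2 points at ρ = 0.5, 0.7 and 0.9.
- The extreme: all 10% fail with a 5 mm Hg rise from 70 (+7.1%), are imputed at −14.3%, and no 30-minute value is used: 0.10 × (7.1 + 14.3) = 2.1.

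**Step 4: effect on error at the margin.** With 38 and 42 observed, SE = 6.65 × √(1/38 + 1/42) = 1.49. A bias of 0.67 raises the one-sided error from 2.5% to P(Z > 1.96 − 0.67/1.49) = 6.5%. A bias of 1.27 raises it to 13%.

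**The case against.** There is a fair case on the other side, and parts of it stand.

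- **The 85% needs its condition.** A reader might take it as a general property of the check. It belongs to about 4 missing per arm. The 10% is a sample-size allowance, and with 1 missing per arm the figure is about 34%.
- **The check is meant to be extreme.** It is a labelled sensitivity analysis and does not decide noninferiority. Passing it would be strong evidence. This stands, and is a reason to keep it as a bound.
- **The 2.1-point figure is not an estimate.** One might infer that the primary analysis flatters HVNI by half the margin. The patient in that example meets the criterion of a 5 mm Hg rise at 30 minutes, so a 30-minute PaCO2 exists and the plan puts it in the imputation model. The example also makes every missing value a failure, although refusal and analyzer faults are listed, and it borrows −14.3% from the plan's NIPPV illustration; the HVNI illustration is −10.0%.
- **The direction is not established.** One might infer that the primary analysis must favour the arm with more failures. A patient who was crossed over or intubated is on rescue support at 60 minutes. If the target is PaCO2 regardless of rescue, nothing in the documents says that value is worse than a responder's.
- **An event indicator may be hard to estimate.** If these events are what remove the gas, few such patients have an observed outcome to learn from.
- **Failures are reported elsewhere.** Treatment failure, conversion and intubation are compared by arm, so an imbalance would be visible. It would still not be carried into the primary estimate.
- **This may be detail for an analysis plan that is not shown, and the lists may be open-ended.** That would answer a complaint about a mere omission. Here the article prints a specific variable list directly after naming causes that the list does not reflect, and it specifies the sensitivity analyses too.

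**Conclusion.** The point holds in a limited form. The stated imputation model does not use the crossover and intubation events that the same section gives as causes of missingness, and its proxies may be absent for the earliest failures. Complete-case and per-protocol analyses drop the same patients. At the planned 10% missingness the one pessimistic check fails in about 85% of trials with equal arms. This assumes normal data, within-arm extremes and missingness unrelated to outcome; the figure is about 55% at 2 missing per arm and 34% at 1, against 16% with none.

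Bias in the primary estimate is possible, but its size and direction are not fixed by the documents. They depend on how many patients fail before 30 minutes and on whether the target is PaCO2 with or without rescue. Under assumed values the HVNI mean could be flattered by roughly 0.2 to 1.3 points; 2.1 is an upper illustration only. The plan should be changed because a more informative analysis is available from data already being recorded. The stated plan has not been shown to give a wrong answer.

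**What to change.** 1. State whether the primary target is 60-minute PaCO2 regardless of rescue. If so, say that any 60-minute gas obtained after crossover or intubation is used in the intention-to-treat analysis.
2. Add crossover, intubation or failure before 60 minutes, and 30-minute pH, to the imputation model, provided enough such patients have an observed 60-minute value to estimate the terms.
3. Prespecify a delta-adjusted tipping-point analysis. Shift the imputed values that are missing because of failure in the HVNI arm, and also vary the shift in the NIPPV arm. Leave values missing through refusal or technical fault under missing at random. Report the delta at which the upper confidence limit crosses 4.3. This is the essential step, because it does not rely on failures having observed outcomes.
4. Keep worst/best imputation, described as an extreme bound.

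The cost is some analysis wording and a few more model runs. Crossovers and intubations are already logged with time and reason, and pH is on the analyzer printout. The result may look slightly less favourable to HVNI. With 19 of 84 patients enrolled as of July 2026 and analysis not begun, the change can still be made credibly in advance.
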